### Safety and adverse events

AEs are undesirable experiences occurring to participants during the trial, whether or not they are considered to be related to the experimental treatment. All AEs during the study must be recorded on the CRF, including the nature of each event, time and date of onset, duration, intensity, seriousness criteria, an assessment of its cause, the need for specific therapy, the actions taken and its outcome. According to the severity of AEs, the investigator will determine whether the participant should be withdrawn from the study, and follow-up procedures should be performed and recorded in detail. The relationship between the experimental treatment and the AEs should be assessed and recorded by the investigator.

A SAE is defined as any untoward occurrence or effect that causes death, is life-threatening, requires prolonged hospitalization, results in persistent significant disability, or leads to a congenital anomaly or birth defect. If a SAE occurs, the investigator must immediately report it to the principal investigator and the ethics committee, and record it on the CRF with a signature and date. The classification of the severity of AEs and relationship to the studied drug are conducted according to our previous study [18].

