**Fig. 1 Fig1:**
[figure not shown]
The flow diagram of this trial

**Table 1 Tab1:** Data collection schedule and measures

Period	Run-in period	Treatment period		Follow-up period		
Day	0	7 ± 2	14 ± 2	30 ± 5	60 ± 5	90 ± 3
Informed consent	×					
Inclusion/exclusion criteria	×					
Medical history	×					
UCG	×					
TOAST	×					
Medical examination	×	×	×	×	×	×
Concomitant medications	×	×	×	×	×	×
Outcomes						
BI scale	×	×	×	×	×	×
mRS scale	×	×	×	×	×	×
NIHSS	×	×	×	×	×	×
Chinese medicine symptom scales of “*Xueyu Zheng*”	×	×	×	×	×	×
EQ-5D scale	×	×	×	×	×	×
Global disability on mRS						×
New-onset major vascular events						×
Overall mortality						×
Incidence of severe hemorrhages						×
Incidence of moderate hemorrhages						×
AEs and SAEs						×
Profiles of microRNA in 60 patients from certain centers	×		×			×
Profiles of mRNA in 60 patients from certain centers	×		×			×

*UCG* ultrasound cardiogram, *TOAST* Trial of Org 10 172 in Acute Stroke Treatment, *BI* Barthel Index, *mRS* modified Rankin Scale, *NIHSS* National Institutes of Health Stroke Scale, *AEs* adverse events, *SAEs* serious adverse events, *microRNA* micro-ribonucleic acid, *mRNA* messenger ribonucleic acid

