#### Secondary outcomes

The total score of Chinese medicine symptom scales of “*Xueyu Zheng*” (blood stasis syndrome).The proportion of patients with the Barthel Index (BI) score of ≥90. BI uses ten variables to describe the activities of daily living (ADL) and mobility, and a higher number is associated with a better performance of ADL [14].The proportion of patients with an improvement in the NIHSS score of ≥4 or the NIHSS score of 0–1. NIHSS is a tool used to objectively quantify the impairment caused by stroke. A NIHSS score of 0 typically indicates normal function in that specific ability, while a higher score is indicative of some level of impairment [15].The quality of life measured by the EQ-5D scale. The EQ-5D scale has five standard dimensions to measure the generalized health-related quality of life [16].Global disability (mRS ≥3) at day 90.Incidence of new-onset major vascular events within 90 days. Major adverse vascular events include ischemic stroke, hemorrhagic stroke, transient ischemic attack, myocardial infarction and vascular-related death.The safety of DHI is evaluated by the incidences of global disability (mRS ≥3) at day 90, new-onset major vascular events, severe hemorrhages and moderate hemorrhages within 90 days. The definition of “severe hemorrhages” and “moderate hemorrhages” is in accordance with the GUSTO bleeding criteria [17]. Other safety measures include the overall mortality at day 90. All the adverse events (AEs) and serious adverse events (SAEs) within 90 days should be observed and documented. Other outcome measures include the changes in the mRNA and microRNA profiles in 60 patients selected from certain centers. An overview of the measurement data collection schedule is shown in Table 1.

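### The SAE definition names prolonged hospitalization but not new admission, so readmissions during follow-up could be classed as non-serious; Table 1 also needs aligning with the text on AE recording

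*Protocol article*

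**What the plan says.** **Definition.** The section on safety and adverse events lists what makes an event serious: death, threat to life, or that it "requires prolonged hospitalization, results in persistent significant disability, or leads to a congenital anomaly or birth defect". The list is presented as complete.

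**Consequence of being serious.** The same section states: "If a SAE occurs, the investigator must immediately report it to the principal investigator and the ethics committee, and record it on the CRF". The section on safety analysis names SAEs as a separate safety measure, analyzed in the safety set.

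**Recording of all events.** The section on safety and adverse events also states: "All AEs during the study must be recorded on the CRF, including the nature of each event, time and date of onset, duration, intensity, seriousness". The entry must further cover cause, therapy, actions and outcome. The section on secondary outcomes adds: "All the adverse events (AEs) and serious adverse events (SAEs) within 90 days should be observed and documented". It also counts "new-onset major vascular events, severe hemorrhages and moderate hemorrhages within 90 days" as safety outcomes in their own right.

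**Schedule.** In Table 1 the row for AEs and SAEs has one mark, at day 90 ± 3. So do the row "Incidence of severe hemorrhages", the moderate-hemorrhage row, and the rows for vascular events, mortality and global disability. The row "Medical examination" is marked at all six visits (days 0, 7, 14, 30, 60 and 90), as is concomitant medication.

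**The concern.** Patients enter as inpatients, so a criterion about prolonging a stay works while they remain in hospital. It stops working at discharge. From then on, an event bad enough to need admission has no existing stay to prolong, and the definition offers no other hospitalization criterion.

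Two things depend on the label. One is the count of SAEs in the safety analysis. The other is immediate reporting, which the protocol attaches to SAEs only. Safety is part of the stated aim of the trial, so the rule that decides what is serious should not change its reach at discharge.

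Table 1 raises a second, smaller matter. A site that works from the table alone finds no prompt for AEs or bleeding at days 7, 14, 30 or 60, although the text tells it to record every AE.

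**Working it through.** No sample size, power or event count enters this point, and the plan gives no figure to reproduce. The check is a reading of the rules against each other.

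**1. Time at risk.** The abstract gives 2 weeks of treatment and 76 days of follow-up: 14 + 76 = 90 days. The share after treatment is 76/90 = 84%. This is a share of calendar time, not of events. Discharge dates are not given, so the share spent out of hospital is unknown.

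**2. A test case.** Take a patient discharged after treatment and admitted again on day 40 for a drug reaction that is not life-threatening and resolves.

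| Criterion as printed | Met? |
|---|---|
| Death | No |
| Life-threatening | No |
| Prolonged hospitalization, read as extending a current stay | No: there is no current stay |
| Prolonged hospitalization, read as needing a long stay | Only if the new stay is long |
| Persistent significant disability | No |
| Congenital anomaly or birth defect | No |

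The hospitalization wording can be read in two ways. A short new admission fails both.

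**3. What happens to that event.**

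| Step | Result under the printed rules |
|---|---|
| Recorded as an AE with onset date | Yes (safety and adverse events; secondary outcomes) |
| Counted among SAEs | No |
| Reported immediately to the principal investigator and ethics committee | No, since that duty applies to SAEs |
| Counted as a hemorrhage or major vascular event | Yes if it meets that outcome's definition, whatever its SAE status |

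The gap therefore lies in classification and expedited reporting. It does not lie in whether the event is captured.

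**4. Table 1 against the text.**

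| Item | Table 1 | Text |
|---|---|---|
| AEs and SAEs | Day 90 only | All AEs during the study, with onset dates; SAEs reported at once |
| Severe and moderate hemorrhages | Day 90 only | Incidence within 90 days |
| Vascular events | Day 90 only | Incidence within 90 days |
| Medical examination, concomitant medications | All six visits | – |

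The text sets continuous recording. The day-90 marks fit a cumulative tally: the hemorrhage rows are titled as incidences, and overall mortality is marked in the same way although deaths would not be discovered only at day 90. What is left is a mismatch between table and text.

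**The case against.** The strongest case against is that the protocol captures these events anyway. Every AE is recorded with its onset and seriousness criteria, SAEs are reported at once, and the Outcome Evaluation Committee evaluates AEs. Bleeding, vascular events and deaths are counted without regard to the SAE label. The article is also a condensed text: the printed phrase may compress a longer criterion, and the list behind the seriousness field on the CRF is not shown.

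Most of this stands, and it limits the point. It does not remove it. The article does not leave the definition to another document; it prints a list, and the list is too narrow. Recording an event as a non-serious AE does not put it in the SAE analysis or start immediate reporting.

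A reader might go further in three ways, none of which the document supports.

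- *Harms overall are under-counted, or a true excess is hidden.* The text requires all AEs to be recorded, and one definition applies to both blinded arms. No mechanism is shown that would hide a difference in total AEs, bleeds or deaths.
- *Events in the infusion period are first elicited about 11 weeks later* (76/7 = 10.9 weeks from day 14 to day 90). This follows only if the recording and reporting rules are ignored. The investigator's decision on withdrawal according to AE severity also presupposes learning of AEs as they occur.
- *Up to about 169 patients would have no AE assessment* (0.20 × 846 = 169). This assumes that no dropout has any AE recorded before leaving, which contradicts the text. The plan's own allowance is in any case 846 − 703 = 143.

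**Conclusion.** The point holds for the SAE definition. As printed, a new admission after discharge that meets no other criterion is a non-serious AE, so SAEs could be under-classified and some would miss immediate reporting. The size cannot be stated: the document gives no AE, SAE or readmission rates and no discharge dates. The 84% of the window that follows treatment shows only that there is ample time for such admissions.

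The conclusion assumes that sites apply the printed wording literally and that the CRF's seriousness list does not already include new admission. If that list does, the article needs only a wording correction.

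The Table 1 part is an inconsistency to be reconciled. It is not evidence that harms go unrecorded.

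**What to change.** **Definition.** Replace the hospitalization criterion with: *requires inpatient hospitalization or prolongation of existing hospitalization*. Use the same wording in the CRF's seriousness field. The cost is one phrase and slightly more SAE reports. Recruitment is under way, so apply the new criterion also to AEs already recorded where the records show an admission, while blinded, so that one definition covers the whole trial.

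**Table 1.** Either mark AEs/SAEs, severe and moderate hemorrhages and vascular events at days 7, 14, 30, 60 and 90, or add a footnote that the day-90 mark is the cumulative 90-day count and that recording is continuous. The visits already take place, so the first option costs at most a CRF page at each, and the second costs a sentence.

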### Data collection and management

An overview of study visits and data collection schedule of this study is shown in Table 1. All data will be recorded by trained clinical investigators in a standardized electronic case report form (e-CRF) via the Brightech-Magnsoft Clinical Information Management Systems (CIMS, Brightech-Magnsoft Inc., Somerset, NJ, USA). To ensure the accuracy and reliability of the data, the study monitor will verify and cross-check the eCRFs against the investigator’s source document records and drug-dispensing log. In case of any discrepancies in the cross-check procedure, the results will be sent to the investigator for resolution. Except for the treatment code, any individual identification of the subjects will not be released until the database is closed.

To guarantee the validity and integrity of the trial design, three committees have been established by the multicenter trial coordination group. The first is the Clinical Trial Guidance Committee, which is responsible for the study design and the implementation process. The second is the DMC (also known as DSMB, Data and Safety Monitoring Board), which will supervise the data collection process in order to control its quality. The third is the Outcome Evaluation Committee (OEC), which will evaluate the key outcomes (including outcome measurements and AEs) based on clinical expertise.

### Statistical analysis

Statistical analysis will be performed by the Statistical Analysis System (SAS, Version 9.1, SAS Institute Inc., Cary, NC, USA). Except for the microRNA and mRNA profiles, most outcome measurements will be analyzed using full analysis sets (FAS) and per protocol sets (PPS), according to intention-to-treat (ITT). Compliance analysis will be based on the FAS, and analysis of concomitant medications will be based on the safety set (SS). Analytical statistics to estimate the difference in the number of participants who have completed or been withdrawn from the trial between groups will be calculated. Baseline characteristics will be summarized by means of simple descriptive statistics. For parametric tests, the results will be described as mean (standard deviation), maximum, minimum, and median, and nonparametric test median (quartile deviation). Categorical data will be described by absolute values and proportion.

Enumeration data will be analyzed by chi-square test (χ^2^ test) test, Cochran-Mantel-Haenszel (CMH) χ^2^ test, Fisher’s exact test, or Wilcoxon rank test. Quantitative data will be compared by analysis of variance (ANOVA) and *t* test. Two-sample *t* tests will be employed for comparison between groups. Paired *t* test will be used to analyze significant difference between pre- and post-treatment. Student-Newman-Keuls (SNK) significance test will be used for pairwise comparison. Chi-squared test will be used for nominal categorical data, rank sum test for ordinal categorical data. The analysis of covariance (ANCOVA) will be used to control potential confounding variables. In all analyses, statistical uncertainty will be expressed by means of 95 % CI.

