#### Inclusion criteria

Female or male inpatients.Aged 18–70 years.Clinical diagnosis of ischemic stroke causing a measurable neurological deficit defined as impairment of language, motor function, cognition and/or gaze, vision or neglect. Ischemic stroke is defined as an event characterized by the sudden onset of an acute focal neurologic deficit presumed to be due to cerebral ischemia after computed tomography (CT) scan excludes hemorrhage.Clinical diagnosis of “*Xueyu Zheng*” (blood stasis syndrome) defined as a total score of Chinese medicine symptom scales of “*Xueyu Zheng*” in ischemic stroke ≥20. The Chinese medicine symptom scales of “*Xueyu Zheng*” include the visual analogue scales (VAS) for the following items: (1) hemiplegia (0–10), (2) numbness of limbs (0–10), (3) dark face (0–9), (4) purple or dark lip (0–8), (5) rough skin (0–4), (6) pain with fixed point (0–5), (7) purple or dark tongue (0–10), (8) ecchymosis on the tongue (0–10), (9) purple sublingual vessels (0–10), (10) sublingual varices (0–8), (11) unsmooth pulse (0–8), and (12) intermittent pulse (0–1).Onset of symptoms within 1 week prior to initiation of study drug administration.Clinical diagnosis of cerebral anterior circulation obstruction.4 ≤ National Institutes of Health Stroke Scale (NIHSS) score <20.Patients willing to participate voluntarily and to sign a written informed consent document. Informed consent will be obtained from each patient or the subject’s legally authorized representative or relatives, or deferred where applicable, according to the regulatory and legal requirements of the participating centers.

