#### Efficacy analysis

Primary and secondary efficacy measures will be analyzed. Any factors impacting efficacy should be taken into account as covariance, such as age and gender. The ANCOVA model, Cox’s proportional hazards regression model, or logistic regression model will be used to assess treatment effects.

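### The Statistical analysis section puts the per-protocol set under the intention-to-treat label and tests within-arm change for significance, which says nothing about the effect of DHI

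*Protocol article*

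**What the plan says.** Three statements in the Statistical analysis section matter here.

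- On analysis sets: "most outcome measurements will be analyzed using full analysis sets (FAS) and per protocol sets (PPS), according to intention-to-treat (ITT". The FAS and the PPS share one clause and one label.
- On change over time: "Paired *t* test will be used to analyze significant difference between pre- and post-treatment". This is worded as a significance test, not as description.
- On multiple comparisons: "Student-Newman-Keuls (SNK) significance test will be used for pairwise comparison". No factor or number of levels is given.

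The article also provides for the randomised comparison. For quantitative data, two-sample t "tests will be employed for comparison between groups". ANCOVA is named for control of confounders. The Efficacy analysis section lists ANCOVA, Cox "or logistic regression model will be used to assess treatment effects", with age and gender as examples of covariates.

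The Design section describes two arms, 2:1 allocation and a superiority aim. The primary outcome is a proportion, mRS 0–1 at day 90. The secondary outcomes include the blood-stasis symptom score, which the Abstract describes as a change, and EQ-5D. Table 1 records both at day 0 and at five later visits. The Inclusion criteria require a total blood-stasis score "in ischemic stroke ≥20".

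**The concern.** **The label.** Intention-to-treat means that patients are analysed in the arm to which they were randomised, whatever happened afterwards. A per-protocol set is formed by excluding patients on what happened afterwards. The two terms cannot describe the same analysis. In a superiority trial the ITT-type analysis is the one that randomisation protects. A PPS result reported under that name would claim a protection it does not have. Exclusion related to treatment is conceivable here: the Safety and adverse events section makes withdrawal depend on the severity of adverse events, and the Sample size estimation section allows for 20% dropout.

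**The paired tests.** Patients enter within a week of a stroke and receive standard care, so most measures should improve in both arms. The blood-stasis score must also be at least 20 at entry, so part of its later fall is regression to the mean. A paired test within the DHI arm asks whether the mean change differs from zero, and recovery alone is enough to make it differ. At stake is a set of significant p values for secondary outcomes that a reader could take as evidence for DHI.

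**Working it through.** **Figures in the plan.** The point rests on no stated number, and the planned size is not in dispute. With 45% against 55%, one-sided α = 0.05, power 0.80 and 2:1 allocation, the fixed-sample total with unpooled variance is 3 × (0.45×0.55 + 0.55×0.45/2) × (1.645 + 0.842)² / 0.10² = 688.6. The inflation factor for three looks under Lan-DeMets O'Brien-Fleming spending is 1.0203, and 688.6 × 1.0203 = 702.6, the stated 703. The proposed change leaves this figure as it is.

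**Paired test with no drug effect.**
- From the plan: 282 placebo and 564 DHI patients (Sample size estimation).
- Assumed: a two-sided 5% test and the same standardised mean change d, in SDs of the change, in both arms.
- The smallest observed mean change that reaches p < 0.05 is about 1.96/√n. This is 1.96/√282 = 0.117 SD on placebo and 1.96/√564 = 0.083 SD on DHI. After 20% loss in the placebo arm (about 226 left) it is 1.96/√226 = 0.130 SD.
- The probability of significance comes from the noncentral t distribution with noncentrality d√n:

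| Common change d | Placebo, n = 282 | DHI, n = 564 |
|---|---|---|
| 0.1 SD | 0.39 | 0.66 |
| 0.2 SD | 0.92 | 0.997 |
| 0.3 SD | 0.999 | >0.999 |

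From 0.2 SD upwards, significance in both arms is close to certain although the drug does nothing. At 0.1 SD the larger arm has the advantage. The chance that DHI is significant while placebo is not is 0.66 × (1 − 0.39) = 0.40, only because the DHI arm is twice the size.

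**Per-protocol set with no drug effect.**
- Assumed: a true favourable rate of 45% in both arms, 20% excluded from each arm, and random exclusion on placebo.
- Let f be the share of unfavourable outcomes among excluded DHI patients. The rate among the DHI patients who remain is (0.45 − 0.20 × (1 − f)) / 0.80.
- The remaining numbers are about 0.8 × 564 = 451 and 0.8 × 282 = 226.

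| f | DHI rate in PPS | One-sided error at nominal 5% |
|---|---|---|
| 0.55 (random) | 45.0% | 0.05 |
| 0.60 | 46.25% | 0.09 |
| 0.65 | 47.5% | 0.15 |
| 0.70 | 48.75% | 0.23 |

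For f = 0.65 the difference is 0.025 and the standard error is about 0.0407 under the pooled null and 0.0406 unpooled. Then (1.645 × 0.0407 − 0.025)/0.0406 = 1.03, with upper tail 0.15. The excess comes wholly from the assumed imbalance in exclusions, which could equally run against DHI.

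**SNK with two arms.** SNK compares ranked means by the studentised range. Two groups form one pair, for which the range statistic is √2 times the two-sample t. SNK is then the two-sample t test under another name.

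**The case against.** The strongest reply is that the randomised comparison is already planned. The section assigns between-group tests to quantitative and count data, and the Efficacy analysis section assigns treatment effects to regression models. Nothing says that a within-arm p value counts as efficacy. A paired t test cannot be applied to the binary primary outcome. Regression to the mean affects both arms alike and does not bias the comparison between them. All of this stands, and it confines the paired-test concern to the quantitative secondary outcomes. It does not make the paired test useful: it is still prescribed as a significance test, and its result carries no information about DHI.

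On the label, the ITT phrase may be compressed wording meant for the FAS only. The definitions of the sets, and which of them leads, may sit in a full protocol or analysis plan that is not shown, so their absence is no finding. That also stands. The sentence as printed is nevertheless untrue of the PPS.

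A reader might infer more than the text supports:

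- *That the trial has two primary answers.* The article says that most outcomes are analysed on both sets. It nowhere calls the PPS primary or co-primary.
- *That SNK lets natural recovery pass for efficacy.* Nothing makes it a within-arm or across-visit procedure, and with two arms it is merely redundant.
- *That 20% dropout, 0.20 × 846 = 169 patients, measures the harm from the PPS.* A patient who drops out without a day-90 mRS also has no observed outcome in the FAS, so the figure does not isolate a per-protocol problem.

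**Conclusion.** The concern holds in a limited form. The ITT label is wrong for the per-protocol set and should be corrected, because this is a superiority trial and the label marks which analysis randomisation protects. The paired t tests should not be used for inference. For the blood-stasis score and EQ-5D they reflect change that is expected in both arms. Under an assumed common change of 0.2 SD they would be significant on placebo with probability 0.92.

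The sizes depend on assumptions that the document does not supply: the standardised change, and unequal exclusion from the PPS. With random exclusion the PPS error rate stays at 0.05, and the article gives no evidence that exclusion will be unequal. The documents do not support the reading that the primary result can arise from natural recovery. The mislabelled PPS matters only if its result is relied on as the ITT result, and the paired tests matter only if within-arm p values are presented as efficacy. The correction is worthwhile because it removes both possibilities at almost no cost.

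**What to change.** In the Statistical analysis section:

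1. Apply the ITT label to the FAS only, with patients analysed as randomised. State that the superiority conclusion rests on the FAS and that the PPS analysis is supportive.
2. Remove the paired t tests as significance tests. Report within-arm change descriptively, as a mean with its SD or interval, without p values.
3. For the blood-stasis score and EQ-5D, replace the unadjusted two-sample t test by the between-arm ANCOVA that the article already names, with the outcome's own baseline value as covariate. The present examples, age and gender, do not exclude the baseline value, but it should be named.
4. Delete SNK, since two arms give only one pair.

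The cost is wording. Table 1 shows that both outcomes are already measured at day 0, so no data, visits or patients are added and the sample size is unchanged.
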